# Intratympanic versus intravenous corticosteroid treatment for sudden sensorineural hearing loss in diabetic patients: proposed study protocol for a prospective, randomized superiority trial

**DOI:** 10.1186/s13063-020-4077-x

**Published:** 2020-02-03

**Keywords:** Sudden sensorineural hearing loss, Diabetes, Randomized controlled trial, Intratympanic methylprednisolone, Intravenous methylprednisolone

## Abstract

**Background:**

Diabetes mellitus is associated with risk of sudden sensorineural hearing loss (SSNHL). Systemic and intratympanic corticosteroids are the two primary treatments for SSNHL in patients with diabetes mellitus. The benefit of intratympanic compared to systemic treatment is the reduced systemic steroid exposure and associated systemic adverse effects. Intratympanic corticosteroid administration may have potential benefits over standard systemic therapies.

**Methods/design:**

The proposed study is a prospective, randomized superiority trial. A total of 96 patients (48 in each group) will be randomized into the experimental or control group. Patients in the experimental group will receive four 1-mL doses of 40 mg/mL of methylprednisolone over a 1-week period, with a dose administered every 2 days via tympanic membrane injection into the middle ear. The control group will be administered intravenous methylprednisolone (1 mg/kg/day, maximal dose 60 mg/day) for 5 days. The primary outcome for this study is the change in hearing threshold from the first audiogram to the 30-day follow-up audiogram. Secondary outcome measures will include pure-tone average (PTA) at 90-day follow up, visual analog tinnitus scale, visual analog vertigo scale, visual analog aural fullness scale, fasting blood glucose and 2-h postprandial blood glucose during treatment, and the change in glycosylated hemoglobin (HbA1C) levels. Vital signs and otological physical examination will be performed at each follow-up visit.

**Discussion:**

The efficacy and safety of intratympanic methylprednisolone compared to intravenous methylprednisolone will be investigated in patients with diabetes mellitus and SSNHL. This trial may provide strong evidence for the efficacy and safety of intratympanic corticosteroid treatment and important clinical information for the treatment of patients with diabetes mellitus and SSNHL.

**Trial registration:**

ChiCTR, ChiCTR1800015954. Registered on 2 May 2018, Retrospectively registered, http://www.chictr.org.cn/showproj.aspx?proj=25326.

## Background

Sudden sensorineural hearing loss (SSNHL) is usually defined as a sensory neural hearing loss greater than 30 dB across three contiguous pure-tone frequencies occurring within 72 h [1]. The annual incidence of SSNHL is 27 per 100,000 in the USA [2]. Diabetes mellitus is a risk factor as well as a poor prognostic factor for SSNHL [3]. The incidence of SSNHL is 1.54-fold higher in patients who have diabetes mellitus compared to patients who do not [4]. Although the standard treatment for SSNHL is systemic corticosteroid administration, this treatment results in loss of glycemic control in patients with diabetes mellitus.

Long-term hyperglycemia in patients with diabetes mellitus may lead to microangiopathy of the inner ear, which results in sensorineural hearing loss [5]. Previous animal and human studies have demonstrated that hair cell loss is observed in the temporal bone as well as thickened and damaged capillary walls of the stria vascular in animals and humans with diabetes mellitus [6]. Several studies have demonstrated that systemic corticosteroid administration in patients with diabetes mellitus and SSNHL had no advantage in hearing improvement when compared to other treatments [7–10]. Moreover, the use of systemic corticosteroids may result in side effects such as insomnia, weight gain, gastritis, mood changes, photosensitivity, and hyperglycemia [1]. Hyperglycemia may further affect the prognosis in SSNHL and patients with diabetes mellitus may be required to increase their insulin intake [9].

An alternative treatment strategy for SSNHL is intratympanic corticosteroid administration via direct injection into the middle ear [1]. Intratympanic treatment may increase drug concentration to the target organ. Parnes et. al. demonstrated higher inner ear corticosteroids levels after intratympanic corticosteroid administration compared to systemic administration in animal models [11]. A multi-center, randomized controlled trial in 250 patients involved comparison of intratympanic versus systemic corticosteroid therapy for SSNHL: the improvements in hearing outcomes were equivalent [12]. The benefit of intratympanic compared to oral treatment is reduced systemic steroid exposure and associated systemic adverse effects [1, 12]. A non-prospective randomized controlled trial that compared systemic versus intratympanic corticosteroid treatment showed improved hearing outcomes in patients with diabetes mellitus and SSNHL.

Based on the evidence of potential advantages of intratympanic over standard systemic therapy, we will perform a randomized superiority trial comparing the efficacy of systemic versus intratympanic methylprednisolone administration in patients with diabetes mellitus and SSNHL. The results of the study may provide evidence to determine whether intratympanic corticosteroid administration is a better primary treatment option for patients with diabetes mellitus and SSNHL.

## Method/design

### Design and setting

This study will be a randomized controlled trial that will be performed at the Peking University Shenzhen Hospital in China. We will enroll 86 patients with diabetes mellitus and SSNHL over a 3-year period. Study participants will be randomized at a ratio of 1:1 to receive either intratympanic methylprednisolone or intravenous methylprednisolone (Fig. 1). The study protocol will follow the Standard protocol items: recommendation for interventional trials (SPIRIT) recommendations for interventional trials (Additional file 1).

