### Sample size calculation

The purpose of the proposed study is to compare the effectiveness of PTA by one-sided *t* test, which is used with the 95% confidence interval method. The difference in PTA is reported in previous publications as 30.7 in the experimental group and as 28.7 in the control group. The difference in the mean was 2, and the combined standard deviation was 3. The type 1 error was 2.5% and statistical power was 90%. Considering a 5% loss rate, 96 samples are required. This allows for 48 participants in the study group and 48 in the control group.

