### Trial status

Protocol version 1.0; 22 September 2017. Recruitment began on 1 March 2018 and will be completed by June 2022.

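### The enrolment target is 86 in one section and 96 in two others; 86 misses the stated 90% power, and 96 does not contain the stated 5% loss allowance

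*Protocol article*

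**What the plan says.** Three places in the protocol article give the trial's total size.

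- Abstract, Methods/design: "A total of 96 patients (48 in each group) will be randomized into the experimental or control group".
- Method/design, Design and setting: "We will enroll 86 patients with diabetes mellitus and SSNHL over a 3-year period".
- Sample size calculation: "Considering a 5% loss rate, 96 samples are required", followed by "This allows for 48 participants in the study group and 48 in the control group".

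Only the Sample size calculation section derives a number. Its inputs are a one-sided t test ("The purpose of the proposed study is to compare the effectiveness of PTA by one-sided"), "The difference in the mean was 2, and the combined standard deviation was 3", and "The type 1 error was 2.5% and statistical power was 90" percent. The allocation ratio is 1:1.

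On timing, Design and setting gives three years, while Trial status says "Recruitment began on 1 March 2018 and will be completed by June 2022". The Discussion adds that a pilot ran from March 2018 to February 2019.

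**The concern.** A trial can have only one enrolment target. Here the operative design section gives a total 10 patients below the one the calculation supports. No text presents 86 as the number of completers, an evaluable subset or a revised target. The Discussion says the pilot bore out the sample size calculation, so it offers no reason for a reduction.

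The target is the only end to recruitment that the article states. If 86 is the figure acted on, the trial runs below the power it claims, and a null result would be less informative than readers are told. If 96 is the figure acted on, the article still claims that it covers 5% loss, and that claim also needs checking.

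**Working it through.** **Inputs** (Sample size calculation): difference δ = 2, SD σ = 3, one-sided α = 0.025, power 0.90, loss 5%, equal arms.

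**Step 1: reproduce the stated 96.** By the normal approximation, the number per arm is

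n = 2 × [σ(z₁₋α + z₁₋β)/δ]² = 2 × [3 × (1.960 + 1.282)/2]² = 47.28, rounded up to 48.

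The total is 96, which matches the article exactly. No loss allowance has been applied at this point. The exact noncentral t calculation gives 49 per arm, 98 in total.

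**Step 2: add the stated 5% loss.**

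- Normal approximation: 48/0.95 = 50.5, so 51 per arm, 102 in total.
- Exact t: 49/0.95 = 51.6, so 52 per arm, 104 in total.

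The stated 96 is therefore the figure before loss.

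**Step 3: power at each target.** The normal approximation is power = Φ(δ/(σ√(2/n)) − 1.960). For 43 per arm, 2/(3 × √(2/43)) = 3.091, and Φ(3.091 − 1.960) = Φ(1.131) = 0.871. The other cells follow in the same way, with noncentral t values alongside.

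| Enrolled | Evaluable | Power, normal | Power, exact t |
|---|---|---|---|
| 86 | 86 (no loss) | 87.1% | 86.3% |
| 86 | 81.7 (5% loss) | 85.4% | 84.5% |
| 96 | 96 (no loss) | 90.4% | 89.8% |
| 96 | 91.2 (5% loss) | 88.9% | 88.3% |

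**Step 4: cost of 86 against 96 on the same basis (exact t).**

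- No loss: 89.8 − 86.3 = 3.5 points. Type II error goes from 10.2% to 13.7%.
- After 5% loss: 88.3 − 84.5 = 3.8 points. Type II error goes from 11.7% to 15.5%.

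**Step 5: can 86 be explained?** Removing 5% from 96 leaves about 91, not 86. Removing 10% leaves 86.4, but the stated loss is 5% and the sentence is about enrolment. A one-sided 5% test with the exact t formula needs 40 per arm; 40/0.95 = 42.1, rounded up to 43, which gives 86. That may be its origin, but it is conjecture, because the article fixes the type 1 error at 2.5%.

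**Step 6: recruitment period.** March 2018 to June 2022 is about 52 months. Taking out the 12-month pilot leaves about 40 months, against 36 for a 3-year period.

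**The case against.** The best defence is that 86 is a slip. It appears once, with no per-arm split and no derivation, while 96 appears twice with both groups given. If 96 was always intended, correcting one digit removes the contradiction and no analysis changes. That is plausible, but the article does not say so, and the correction would still leave a 96 that is described as covering 5% loss when it does not.

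Several stronger readings are tempting and are not supported:

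- A reader might infer that 96 is the validated figure and only 86 is wrong. Step 2 shows that neither target delivers 90% after the stated loss, although 96 comes within two points.
- A reader might infer that the type II error rises from 10% to about 15%. That sets 86 after loss against a nominal figure that 96 itself does not reach after loss. The like-for-like change is the one in Step 4.
- A reader might infer that two targets let the sponsor stop at whichever looks better. The Randomization and blinding section leaves participants, physicians and paramedics unblinded, but it blinds investigators, outcome assessors and statisticians until the end of the study. No interim look is described. Data-driven stopping is speculation.
- A reader might treat the recruitment period as a second clear contradiction. The pilot occupies the first 12 months of the longer window, and the article does not say whether its patients count, so this is an ambiguity.
- A reader might assume that the registry record and the flow chart carry the wrong number. Neither can be seen here.

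**Conclusion.** The contradiction between 86 and 96 is explicit and unexplained. At 86 the power falls short of the stated 90% by about 3 to 4 points with no loss and about 5 points after 5% loss. At 96 the nominal 90% holds only before loss; after loss the shortfall is about 1 to 2 points.

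These figures rest on the article's assumed 2 dB difference and SD of 3, equal arms and loss of exactly 5%. Whether those assumptions are sound is a separate question: the Sample size calculation section and the Discussion assign 30.7 and 28.7 to opposite treatments. That does not affect the conflict between 86 and 96. The recruitment-period mismatch is minor.

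**What to change.** State one enrolment target throughout. If 96 is intended, replace 86 in Design and setting. In Sample size calculation, give the power that the chosen target delivers after 5% loss: about 88% for 96 (exact t), or about 85% for 86. If 90% after loss is to be kept, the target becomes about 102 (normal approximation) to 104 (exact t), which is 6 to 8 more patients than 96.

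Add a sentence reconciling the 3-year period in Design and setting with the dates in Trial status, and say whether the pilot period and its patients count towards the trial. It would be prudent to check that the flow chart and registry entry show the same number.

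The cost is wording alone if 96 stands with its power restated. Only a decision to hold 90% after loss adds recruitment.

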**Fig. 1 Fig1:**
[figure not shown]
Study flow chart. SSNHL, Sudden sensorineural hearing loss; ITM, intratympanic methylprednisolone; IVM, intravenous methylprednisolone

After receiving written informed consents, patients will be randomly allocated to one of two groups to undergo treatment for 10 days. The follow-up period will be 90 days. This trial protocol was approved by the ethics committees of Peking University Shenzhen Hospital and registered at www.chictr.org.cn on 2 May 2018 (ChiCTR1800015954) under the principal investigator [name].

### Study participants

Patients with diabetes mellitus and a clinical diagnosis of SSNHL will be enrolled into this study. Based on the Clinical Practice Guidelines of the Sudden Hearing Loss of American Academy of Otolaryngology, Head and Neck Surgery Foundation in 2012, SSNHL is defined as a sensory neural hearing loss greater than 30 dB across three contiguous pure-tone frequencies occurring within 72 h [1]. The criteria for the diagnosis of diabetes mellitus is compliant with the Standards of Medical Care in Diabetes-2010 of the American Diabetes Association [13].

Research assistants will introduce and discuss the trial contents with all potential study participants using Mandarin or the local language. After screening, all eligible subjects will be required to sign a consent form and will be provided information on the main aspects of the trial. Patients will then be able to have an informed discussion with their family and participating consultant. Research assistants will then collect signed consent forms from patients willing to participate in the trial.

#### Recruitment procedure

The majority of the study participants will be recruited through posters on the Internet and in hospitals. Recruitment will also be offered to patients via the trial center.

#### Inclusion criteria

Patients will be enrolled if they have a clinical diagnosis of SSNHL with diabetes mellitus. SSNHL is defined as a sensory neural hearing loss greater than 30 dB across three contiguous pure-tone frequencies of pure tone audiometry occurring within 72 h. A diagnosis of diabetes mellitus will be based on the Standards of Medical Care in Diabetes-2010 [13]. Pure-tone average (PTA) will be calculated using the arithmetic mean of the hearing thresholds at 500, 1000, 2000, and 4000 Hz in the affected ear. Patients must have unilateral SSNHL. Study participants mus be between 18 and 65 years old. The time from onset to admission must be within 30 days and the hearing loss must have been deemed idiopathic following a suitable otolaryngologic evaluation. This will include medical and otologic history and extensive systems review, head and neck otologic and neurotologic physical examination, audiometry, and imaging to rule out structural or retrocochlear conditions, such as vestibular schwannoma, stroke, or demyelinating disease.

#### Exclusion criteria

The exclusion criteria are:
External ear inflammation, tympanitis, or external auditory canal swelling in the ears;Diagnosis of Meniere’s disease in the affected ear, chronic suppurative otitis media or cholesteatoma of the middle ear, or ear sclerosis;History of congenital hearing loss;History of ear barometric injury or trauma;History of drug-induced or syphilitic deafness;Diabetes mellitus combined with history of diabetic foot, diabetic nephropathy, diabetic retinopathy, cerebral hemorrhage, or cerebrovascular embolism;Diabetes mellitus combined with active-phase tuberculosis, rheumatic disease, severe coronary atherosclerosis, severe psychosis, or pancreatitis;Chronic renal insufficiency, severe osteoporosis, alcoholism, head and neck malignant tumor, or history of radiotherapy and chemotherapy;Combined immunodeficiency virus, hepatitis B virus, hepatitis C virus, or herpes zoster virus infection;Use of chemotherapy or immunosuppressant drugs within the first 2 weeks;Allergy to the trial drugs.

### Interventions

Participants in the study group will receive four 1-mL doses of 40 mg/mL of methylprednisolone over 1 week, with a dose administered every 2 days by tympanic membrane injection into the middle ear by an otolaryngologist using an operating microscope: 2% tetracaine solution will be used for local anesthesia. Patients will be in the supine position with the affected ear slightly raised and will remain in this position for 30 min after administration of the injection. Patients will also be required to avoid swallowing and vocalization during the treatment period. Patients in the control group will receive a 1-week treatment with intravenous methylprednisolone (1 mg/kg/day; the maximal dose is 60 mg/day) for 5 days, and then have 2 days off. Good Manufacturing Practice (GMP)-grade methylprednisolone will be purchased from Pfizer Manufacturing, Belgium NV.

#### Rescue and concomitant treatment

All study participants will be hospitalized. During the duration of their treatment, patients will be on a low-salt diabetic diet, and receive medications, including mecobalamine (Eisai China Co., Ltd., 0.5 mg three times per day) and extract of Ginkgo Bilobaleaves (Chi Sheng Pharma & Biotech Co., Ltd., Taiwan, China, 70 mg per day). Glycemic levels will be closely monitored and insulin will be administered if necessary. For patients with serious vertigo after tympanic injection, diphenhydramine (20-mg intramuscular injection per episode) will be used as the rescue drug following the physician’s advice.

### Randomization and blinding

Study participants will be randomly allocated to one of two different treatment groups at a 1:1 ratio using the SAS9.2 software with block randomization; block = 4 or 6. Randomization will be concealed until interventions are assigned and enrollment, follow up, data collection, data cleaning, and analysis are performed. It will not be possible to blind the study participants, physicians and paramedics. The investigators, outcomes assessors, and statisticians will be blinded to treatment allocation, and the allocation will only be revealed at the end of study. The randomization list and blinding codes will be kept strictly confidential.

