### Outcome measures

The primary outcome measure will be the change in PTA (dB) from the first audiogram to the 30-day follow-up audiogram. Hearing will be evaluated using air-conducted and bone-conducted PTA after 1 and 14 days of treatment, and at 30 and 90 days of follow up.

Secondary outcome measures will include PTA at 90 days, visual analog tinnitus scale, visual analog vertigo scale, visual analog aural fullness scale, fasting blood glucose and 2-h postprandial blood glucose during treatment, and the change in glycosylated hemoglobin (HbA1C) levels. Vital signs and otological physical examination will be performed at each follow-up visit (Fig. 2).

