### Safety assessments

Study participants will be requested to report all adverse events (AEs) at each follow-up visit. All AE reports will be recorded and assessed by the investigators. Blood test, urinalysis, hemagglutination test, and electrocardiograph examinations will be performed before and after the treatment. All abnormal changes from baseline laboratory test results will be evaluated. Other safety test parameters will be measured at the discretion of the treating physician and will be based on the patient’s medical history.

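### The blinding stated for investigators and outcome assessors cannot hold for adverse-event assessment or for the three visual analog scales; it is achievable for PTA but not secured in the text

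*Protocol article*

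**What the plan says.** Under Randomization and blinding, the protocol article first concedes what cannot be masked: "It will not be possible to blind the study participants, physicians and paramedics". The next sentence claims masking for everyone else: "The investigators, outcomes assessors, and statisticians will be blinded to treatment allocation", with the allocation disclosed only when the study ends.

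The Interventions section shows why participants and treating staff cannot be masked. The experimental drug is given "by tympanic membrane injection into the middle ear by an otolaryngologist using an operating microscope", whereas "Patients in the control group will receive a 1-week treatment with intravenous methylprednisolone". No sham injection is described for the control group.

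Three other places bear on the claim:

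- Safety assessments: participants report adverse events at each follow-up visit, and "All AE reports will be recorded and assessed by the investigators".
- Outcome measures, primary: "The primary outcome measure will be the change in PTA (dB) from the first audiogram to the 30-day follow-up audiogram". The secondary list has PTA at 90 days, visual analog scales for tinnitus, vertigo and aural fullness, fasting and postprandial glucose, and change in HbA1C.
- Outcome measures, visits: "Vital signs and otological physical examination will be performed at each follow-up visit". The examiner is not named.

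The Discussion states the aim of showing that the intratympanic route is better on both efficacy and safety.

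**The concern.** The blinding sentence is a positive statement about the design, and other sections give the roles it covers tasks that cannot all be done blind. An investigator who records what an unmasked patient reports about an ear injection learns the arm. A patient scoring his or her own tinnitus is the assessor of that outcome and already knows the arm.

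What is at stake is mainly the safety comparison and the symptom scales. Judgements on recording and grading adverse events, and self-rated symptoms, are open to influence from knowing the treatment. If the results are reported under the blinding statement as it stands, the safety comparison, which is half of the trial's stated aim, will appear to have a protection it did not have. For the primary outcome the question is narrower: whether the text keeps the audiometry tester away from the information that would unmask that person.

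**Working it through.** The article gives no figure to reproduce here. The check sets the blinding statement against the task given to each role, then counts the listed outcomes by who generates the measurement.

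**Step 1: adverse events.** Three statements are read together.

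- Investigators are masked until the end of the study (Randomization and blinding).
- Investigators record and assess all adverse events (Safety assessments).
- Participants, who know their arm, report those events (Safety assessments, with the concession on masking).

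Some events carry the route with them. The section on rescue and concomitant treatment provides for serious vertigo following the tympanic injection, an event that by its description can occur in one arm only. The Discussion cites an earlier non-randomized study in which 2 of 34 intratympanic patients (2/34 = 5.9%) had a tympanic membrane perforation. An investigator who records such an event as described knows the arm before the end of the study. For these events the first two statements cannot both be true.

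**Step 2: outcomes by source of the measurement** (from Outcome measures).

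| Source | Outcomes | Share of 8 | Can assessment be blinded? |
|---|---|---|---|
| Audiometry | PTA change to day 30 (primary); PTA at day 90 | 2/8 = 25% | Yes, if the tester is kept unaware |
| Visual analog scales | Tinnitus; vertigo; aural fullness | 3/8 = 37.5% | No, if patient-rated |
| Laboratory | Fasting glucose; 2-hour glucose; HbA1C | 3/8 = 37.5% | Little assessor judgement involved |

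The total is 1 primary plus 7 secondary = 8 outcomes. Blinded assessment is ruled out for 3 of 8, all secondary. The adverse-event comparison is additional to this list.

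**Step 3: the primary outcome.** The section on data management lists physicians and assessors as separate roles, so a masked tester is compatible with the text. However, an ear examination takes place at every follow-up visit, and the article does not say whether the tester is also the examiner or takes the adverse-event report, or in what order these are done. All patients are inpatients during treatment at a single hospital. This leaves a route to unmasking open. It does not show that unmasking occurs.

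**The case against.** The strongest case against the point has four parts.

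1. **The split is openly stated.** The sentence before the blinding claim says that participants and treating staff are not masked. Unmasked patients with masked assessors is a coherent and common arrangement. This stands, and a reader should not infer that the article presents every outcome as blinded. It does not rescue the adverse-event task, which is given to the investigators, who are named as masked.

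2. **Most outcomes are unaffected.** A reader might infer that the stated blinding is absent for most outcomes. The count does not support this: 3 of 8 is a minority. The share reaches 5 of 8 (62.5%) only if both PTA outcomes are counted as unblinded because the responding patient knows the arm, and that is a different matter from whether the tester is masked.

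3. **The threat to PTA is conjecture.** A reader might infer that the ear examination unmasks the audiometry. The article does not say that one person does both, or that a puncture is still visible at day 30 or 90. The written procedures given to staff, and the schedule in Fig. 2, could settle the order and were not available here. This stands in full. The small planned difference of 2 dB does not change it, because the document gives no basis for the size of any tester bias.

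4. **Not every adverse event reveals the arm.** Blood tests, urinalysis and the electrocardiogram do not by their nature show the route. Vertigo alone does not either, since it is measured in both arms. The cited perforations come from another study. This also stands: some events unmask, not all. But a claim that investigators remain masked to the end fails once some of their required tasks reveal the allocation.

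A fuller protocol could separate roles for audiometry. It could not make patient-rated scales blinded, and it would not alter the article's own assignment of adverse-event assessment.

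**Conclusion.** The point holds in a limited form. The article states a property, masked investigators and outcome assessors, that its own task assignments rule out for adverse-event assessment and, if patient-rated, for three of eight listed outcomes, all secondary. The claim is achievable for the primary and 90-day PTA and matters little for the three laboratory outcomes. For PTA the finding is an unsecured safeguard, not a shown failure.

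Two assumptions carry this. The first is that the visual analog scales are rated by the patient, which is usual but not stated. The second is that the investigators who assess adverse events are the masked investigators of the blinding sentence, which is the plain reading because both sections use the same term. No size of bias can be derived from the document. Correction is worthwhile because the safety comparison is part of the trial's stated aim and the change is cheap.

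**What to change.** - **Randomization and blinding:** limit the claim to the audiometry assessor and the statistician, and state for each outcome whether its assessment is masked.
- **Outcome measures and Safety assessments:** label the three visual analog scales and the adverse-event comparison as open-label. State who completes the scales.
- **Discussion:** qualify the intended safety conclusion as resting on open-label assessment.
- **Outcome measures, primary outcome:** state that at each visit with audiometry the audiogram is done before the ear examination and the adverse-event interview, by someone who does neither.

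The cost is an amendment to the wording, a fixed order of procedures within a visit, and a less favourable description of blinding. The article does not describe staffing, so whether a separate audiometry tester is already in place, or would have to be arranged, is for the sponsor to confirm.
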